### Data management

All procedures conform to confidentiality standards for medical data. Authorized medical staff treating the patient is granted unlimited access to the patients’ data, whereas restricted access to anonymized data is granted to other staff and researchers. All data will be entered electronically into specific database developed by CTCTC for this study within 1 week and all original forms or records will be kept at all study sites. Participant trial folders are stored in order and in a secure and accessible place at each study site which will be maintained in storage for a period of 3 years after completion of the study. All data will be performed periodically on the CTCTC backup server.

### Statistical analysis

According to the standard approach of noninferiority trials, the analysis will be conducted with both per-protocol (PP) and modified intention-to-treat (mITT) populations. Noninferiority, defined as a between-group difference of less than 5% in the upper boundary of one-sided 90% Wald confidence interval (which is equivalent to a one-sided significance of 5%) for the proportion of patients with primary unfavorable outcomes, must be shown on both analyses above to declare that either regimen is noninferior. We will use the chi-square test to compare the secondary outcomes of patients’ sputum-culture conversion at the end of 8 weeks (intensive phase) and treatment completion across treatment groups and the log-rank test to compare the time to culture-negative status. Other secondary outcomes will be analyzed with similar methods, including the time to an unfavorable outcome, the outcome at the end of treatment, adverse effect occurring frequency, patients’ adherence and the transition of radiological manifestation. Missing data will be dealt with the last observation carried forward imputation technique. Dropouts and withdrawals from the study will be recorded through the intervention and follow-up periods. When differences in baseline phenotype are present, these differences will be taken into account during analysis of treatment effect between groups, by regarding them as covariates.

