### Sample size assumption

Under the conditions of the trial, we assumed that the standard 6-month regimen has a 95% or higher sputum culture conversion rate and with estimated 92.5% of that for 4.5-month study regimen based on the published data. The study was designed to determine whether either of the shortened study regimens was not inferior to the control regimen and a margin of noninferiority of 5% was used. With the assumption that as many as 20% of patients will loss to follow-up or not be assessable in the primary analysis, and with the consideration of approximately 5.5% primary drug resistance prevalence, a total target sample size was 3900 patients (1300 subjects per group) would be required to demonstrate noninferiority, with a statistical power of 0.8 and an alpha level of 0.05 (one-sided). Participant recruitment began in August 2016 and is expected to finish in December 2018.

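### The noninferiority rule labels its interval one-sided 90% and equates it with one-sided 5% significance; the two cannot both hold

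*Protocol article*

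**What the plan says.** Protocol article, Statistical analysis: a shortened regimen is noninferior if the difference from control in the proportion with a primary unfavorable outcome is below 5% at the "upper boundary of one-sided 90% Wald confidence interval (which is equivalent to a one-sided significance of 5" percent. The interval label and the significance level thus stand in one sentence, the second in parentheses. The criterion must be met in both the per-protocol (PP) and the modified intention-to-treat (mITT) population.

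Protocol article, Sample size assumption: the trial is planned "with a statistical power of 0.8 and an alpha level of 0.05 (one-sided"), and "a margin of noninferiority of 5% was used". Nothing elsewhere in the article corrects or restates the interval.

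**The concern.** The sentence fixes the threshold for the trial's main conclusion, and it describes two different thresholds. An analyst who programs the interval label adds 1.2816 standard errors to the estimate. One who programs the significance level adds 1.6449. The second matches the planned alpha and the first does not.

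At stake is whether an observed deficit that lies between the two thresholds counts as noninferior. Planning already assumes that the shortened regimens are 2.5 points worse than control, so the estimate may well fall near the threshold. The Background and Discussion also report that three earlier 4-month fluoroquinolone trials failed to show noninferiority, so a false acceptance would matter.

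**Working it through.** **Inputs**
- Margin: 5 percentage points (Sample size assumption).
- Control rate: "the standard 6-month regimen has a 95% or higher sputum culture conversion rate", so 5% unfavorable.
- Shortened regimen: "with estimated 92.5% of that for 4.5-month study regimen", read as an absolute rate, so 7.5% unfavorable.
- 1300 patients per group. Losses: "as many as 20% of patients will loss to follow-up or not be assessable in the primary analysis", and about 5.5% primary drug resistance.
- Assumption: the two losses multiply, so 1300 x 0.80 x 0.945 = 983 assessable per arm. The article gives no size for either analysis set.

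**Step 1. The stated equivalence.** The one-sided level of an upper bound at estimate + z x SE is 1 - Phi(z).
- One-sided 90% bound: z = 1.2816, level 0.10.
- Two-sided 90% interval, or one-sided 95% bound: z = 1.6449, level 0.05.

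The article's 5% is not reproduced from its own interval label. It is reproduced once the label is read as two-sided.

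**Step 2. Error of the Wald rule at the margin.** True unfavorable rates 5% and 10%, 983 per arm, exact binomial enumeration, one comparison in one analysis set:
- z = 1.2816: 10.3%.
- z = 1.6449: 5.2%.

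**Step 3. Largest passing observed difference.** Take an observed control rate of 5% and solve d + z x SE(d) = 0.05, where SE(d) = sqrt[(0.05 x 0.95 + (0.05 + d)(0.95 - d)) / 983]. The Wald standard error uses the observed rates, so it changes with d.
- z = 1.2816: d = 3.55 points (SE 1.131; 3.55 + 1.2816 x 1.131 = 5.00).
- z = 1.6449: d = 3.16 points (SE 1.116; 3.16 + 1.6449 x 1.116 = 5.00).

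The band between them is about 0.4 points wide. For example, an observed difference of 3.4 points has SE 1.125, and its bound is 4.84 under the label (passes) and 5.25 under the 5% test (fails).

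**Step 4. Does the sample size show which level was meant?** Evaluable n per arm = (z_alpha + 0.8416)^2 x (0.05 x 0.95 + 0.075 x 0.925) / 0.025^2.
- One-sided 0.05: 1157 evaluable, inflated to 1531 (dividing by 0.80 x 0.945) or 1554 (dividing by 0.745, the losses added).
- One-sided 0.10: 843 evaluable, inflated to 1116 or 1132.

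Neither is close to 1300. Other variance choices come within 3% at either level: the control variance in both arms at 0.05, divided by 0.745, gives 1262; the experimental variance in both arms at 0.10, divided by 0.80 x 0.945, gives 1325. The sample size therefore does not settle the question.

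**Step 5. Power under the planning rates**, 983 per arm: SE = sqrt[(0.0475 + 0.069375) / 983] = 1.090 points, and 2.5 / 1.090 = 2.293.
- z = 1.2816: Phi(2.293 - 1.2816) = 84%.
- z = 1.6449: Phi(2.293 - 1.6449) = 74%.

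If the planning rates are true, the two readings disagree in about 10% of trials, again for one comparison in one set.

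**The case against.** The strongest reply is that the intent is plain. One-sided 5% is stated twice, the upper limit of a two-sided 90% interval gives exactly that level, and only the word before 90% is out of line. This stands as the likeliest explanation. A reader might infer from the label that the trial's type I error is doubled, and the document does not support that: the doubling arises only if the label is followed over both the parenthesis and the sample size section. But the intent has to be inferred, and Step 4 shows that the sample size does not confirm it.

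A second reply is that PP and mITT must both pass, so 10.3% and 5.2% are not error rates of the full rule. This also stands. The joint requirement lowers both figures by an amount that cannot be computed from the document. As an illustration only, suppose both sets lie exactly at the margin and the two test statistics have a correlation of 0.90 to 0.99 (assumed). The joint pass rate is then 6.9% to 9.0% at nominal 10%, and 3.2% to 4.4% at nominal 5%. The ratio stays near two, but neither range is a property of the plan.

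A reader might also enlarge the point by combining the two shortened regimens into one chance of a false claim. That is a question of multiplicity, separate from the interval label, and it is left out here.

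A third reply is that the SAP, which is not shown, may state the interval correctly. It may. The point does not rest on an omission, since the article itself states a false equivalence.

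**Conclusion.** Wrong as written. The interval label contradicts the significance level in its own parenthesis and the design alpha in the sample size section. The cause is most likely a wording slip for the two-sided 90% interval. What is established is an ambiguous primary decision threshold; an inflated test is not established.

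If the label were carried out literally, the nominal one-sided error would be 10% instead of 5% per comparison and per analysis set, and the largest passing observed difference would rise by about 0.4 points. The 10% against 5% follows from the normal quantiles alone. The enumerated error rates and the limits in points also rest on 983 assessable per arm and a control rate of 5% unfavorable. The point deserves correction because it is the noninferiority criterion itself, and the repair is very small.

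**What to change.** Replace the interval wording with: *the upper limit of the two-sided 90% Wald confidence interval (equivalent to a one-sided 95% bound, one-sided alpha 5%) for the difference in unfavorable proportion must be below 5 percentage points in both mITT and PP*. Check that the SAP and the analysis programs say the same.

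The trial is open-label, the data and safety monitoring board reviews efficacy about every 3 months, and an interim analysis is planned, so blinding cannot mark the deadline. The correction should be made and dated before any comparative efficacy analysis is used for the noninferiority decision.

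The cost is one sentence, with no new data. The criterion becomes about 0.4 points stricter than the literal label, and at 983 per arm the power for one comparison in one set is 74% instead of 84%. Against the alpha that the protocol already states, nothing changes.

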### Outcome measures

The primary efficacy outcome measures include the percentage of participants with treatment failure or relapse by 24 months after the end of treatment, percentage of participants with treatment failure at either 4.5 months or 6 months after randomization. The secondary efficacy and safety outcomes include the time to sputum (both smear and culture) conversion within intensive phase of 2 months and the percentage of participants with sputum conversion (both smear and culture) at the completion of treatment, the number of adverse reactions occurring on treatment and during the follow-up period, adherence to treatment and radiological manifestation transition. Of note, treatment failure was defined as sputum smear positive at the end of treatment and relapse after completion of treatment is defined as at least one positive culture in the scheduled follow-up visits in two years. Participants with negative cultures at the end of follow-up are considered to have had a favorable outcome. For all treatment failures and relapses, one culture of a sputum sample obtained before treatment and one culture of a sputum sample obtained after treatment failure or relapse are planned to store at −80 °C and the samples will be sent to national clinical TB reference lab in Beijing Chest Hospital for further research. The detailed observation schedule is present in Table 3.

**Table 3 Tab3:** Assessment schedule – for all patients recruited

Observation/Investigation		Screening	Treatment Phase (weeks)									Follow-up (Post-treatment phase, months)							
Study visits		0	2	4	6	8	12	16	19	22	26	3	6	9	12	15	18	21	24
Time window (days)			±3	±3	±3	±3	±7	±7	±7	±7	±7	±14	±14	±14	±14	±14	±14	±14	±14
Demographics		X																	
Written or witnessed informed consent		X																	
Patients eligible criteria judgement		X																	
Medical history and clinical assessment		X	X	X	X	X	X	X	X	X	X	X	X	X	X	X	X	X	X
Concomitant diseases and medication taken assessment		X	X	X	X	X	X	X	X	X	X	X	X	X	X	X	X	X	X
Randomized assignment		X																	
Efficacy evaluation																			
Bacteriological test	Sputum smear	X	X	X	X	X	X	X	X	X	X	X	X	X	X	X	X	X	X
	Sputum culture	X	X	X	X	X	X	X	X	X	X	X	X	X	X	X	X	X	X
X-ray		X				X			X		X		X		X		X		X
Safety evaluation																			
Complete blood count		X		X		X	X	X	X	X	X								
Urinalysis		X		X		X	X	X	X	X	X								
Hepatic and renal functions		X		X		X	X	X	X	X	X								

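### Last observation carried forward is not barred from the primary endpoint; it scores patients lost after a negative culture as relapse-free and, if loss is similar across arms, makes false noninferiority more likely

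*Protocol article*

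**What the plan says.** The Statistical analysis section names one method for missing data: "Missing data will be dealt with the last observation carried forward imputation technique". The sentence closes a run of text that covers first the primary noninferiority rule and then the secondary outcomes. It exempts neither. The same section requires noninferiority in both the per-protocol (PP) and the modified intention-to-treat (mITT) population.

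Under Outcome measures, the primary endpoint is the "percentage of participants with treatment failure or relapse by 24 months after the end of treatment". It is cumulative, because "relapse after completion of treatment is defined as at least one positive culture in the scheduled follow-up visits in two years". The same section adds: "Participants with negative cultures at the end of follow-up are considered to have had a favorable outcome".

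The Sample size assumption section expects that "as many as 20% of patients will loss to follow-up or not be assessable in the primary analysis".

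**The concern.** Carrying the last value forward suits a relapse endpoint poorly. Under the planning rates (95% and 92.5% success) most patients are culture-negative when treatment ends. If such a patient stops attending, the carried value is negative and becomes a favorable outcome at 24 months, although part or all of the risk period went unseen.

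The period hidden in this way is the one that matters. The protocol's Discussion says that earlier 4-month fluoroquinolone regimens failed through recurrence after treatment, despite fast conversion on treatment. If a similar share of events is hidden in each arm, the arm with more relapses loses more of them. The observed difference shrinks toward zero, and in a noninferiority trial that favors the experimental regimen. The imputed outcomes are also counted as if observed, so the interval does not reflect the loss.

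The rule also fits badly with the sample size section, which describes up to a fifth of patients as lost or not assessable in the primary analysis, whereas carrying forward gives the lost ones an outcome.

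**Working it through.** **Inputs from the protocol**
- Margin 5 points and one-sided alpha 0.05 (Sample size assumption, Statistical analysis). I read the decision limit as the upper end of a two-sided 90% Wald interval, z = 1.6449.
- Control unfavorable rate: 100 − 95 = 5%. At the margin the experimental rate is 5 + 5 = 10%.
- Patients analyzed per arm: 1,300 × (1 − 0.055) = 1,228. This removes the 5.5% with primary resistance and keeps lost patients, since the rule gives them an outcome.
- Loss d = 20%, the planning maximum; 10% is shown as a milder case.

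**Assumed, because the protocol does not give it:** h, the share of lost patients' events that fall after they are lost.

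**Formulas**
- Observed rate = true rate × (1 − d × h).
- D = difference of the observed rates; SE = √[p₁(1 − p₁)/n + p₂(1 − p₂)/n].
- P(declare noninferiority) = Φ[(0.05 − D)/SE − 1.6449].

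**Step 1, no hidden events.** D = 0.050, SE = 0.01058, P = Φ(−1.645) = 5.0%. The plan's nominal rate is reproduced.

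**Step 2, loss spread evenly over 24 months.** Relapse times are taken as exponential, confined to 24 months. A median of 4 months gives h = 0.225; a median of 12 months gives h = 0.388.

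| Loss | Median relapse time | Observed rates | D | P |
|---|---|---|---|---|
| 20% | 4 months | 4.78% vs 9.55% | 4.78 points | 7.7% |
| 20% | 12 months | 4.61% vs 9.22% | 4.61 points | 10.3% |
| 10% | 4 months | 4.89% vs 9.78% | 4.89 points | 6.2% |
| 10% | 12 months | 4.81% vs 9.61% | 4.81 points | 7.2% |

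A visit-based simulation (40,000 trials, 1,300 per arm, 20% loss) gives 9.7% with front-loaded relapse (h = 0.33) and 14.7% with relapse spread evenly over the eight follow-up visits (h = 0.56). Later relapse makes the problem larger.

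**Step 3, extreme under equal loss: all loss at treatment end, all events still to come (h = 1).** With d = 20%, the observed rates are 0.8 × 5% = 4% and 0.8 × 10% = 8%. D = 0.040, SE = 0.00955, P = Φ(1.047 − 1.645) = 27.5%. With d = 10%, P = 12.5%.

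**Step 4, unequal loss (h = 1).**

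| Loss, control / short arm | Observed rates | D | P |
|---|---|---|---|
| 15% / 25% | 4.25% vs 7.5% | 3.25 points | 58% |
| 25% / 15% | 3.75% vs 8.5% | 4.75 points | 8.3% |
| 20% / 10% | 4.0% vs 9.0% | 5.0 points | 5.0% |
| 30% / 10% | 3.5% vs 9.0% | 5.5 points | 1.5% |

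**Step 5, the obvious substitute rule: all missing counted as unfavorable.** With equal 20% loss, the rates are 0.20 + 0.80 × 0.05 = 24% and 0.20 + 0.80 × 0.10 = 28%. D = 4.0 points, SE = 0.01768, P = 14.0%. This also shrinks the difference.

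**The case against.** The strongest reply is that the rule may never have been meant for the primary endpoint. The sentence follows a list of secondary outcomes, and the sample size section speaks of patients who cannot be assessed in the primary analysis. One can read the article so that lost patients leave that analysis and carrying forward fills other gaps. The two analysis populations are not defined, and an article may leave that to the full protocol. This stands as ambiguity. It does not remove the point, because the one method the article fixes carries no exemption.

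A second reply is the dual-population rule. If PP leaves out patients with incomplete follow-up, the joint false noninferiority rate cannot exceed the PP rate, which is about 5% when loss is unrelated to outcome. That is correct, but the article does not state such an exclusion.

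A third reply concerns size. The 28% figure needs the full 20% lost at treatment end and no failures already recorded, yet the endpoint includes failure seen at treatment end. If 30% of events were failures (an assumption), Step 3 becomes Φ[(0.05 − 0.043)/0.00988 − 1.645] = 17.5%, and the 20%-loss rows of Step 2 fall to about 7% to 8%. This stands, and the extreme should not be quoted as the expected size.

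A reader might infer several stronger things that the document does not support:
- That the rule always favors noninferiority. Step 4 shows that heavier loss in control can cancel or reverse the bias.
- That the 58% case is likely. Nothing in the document points to more loss in the short arms; the Background and Discussion expect shorter treatment to help compliance and completion.
- That nobody is left unassessable. Population exclusions, for instance for resistance, can still apply, so this is a tension with the sample size section and not a flat contradiction.
- That every lost patient becomes a success. An earlier positive follow-up culture already counts as relapse, and a patient lost while still positive is carried forward as unfavorable.
- That 20% loss can be set against the 5-point margin as a multiple. One is a proportion missing and the other a risk difference.

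**Conclusion.** The point holds in qualified form. As written, the missing-data rule reaches a cumulative 24-month relapse endpoint and credits unobserved time as relapse-free. With similar loss across arms it biases the comparison toward noninferiority. With 20% loss spread evenly over follow-up and a median relapse time of 4 to 12 months, the false noninferiority rate is about 8% to 10% instead of 5%; with 10% loss it is about 6% to 7%. About 28% is the upper bound for equal 20% loss that is unrelated to outcome.

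These figures rest on a true difference at the margin, 1,228 patients per arm, assumed relapse timing, no events already recorded as failures, and neither population leaving out lost patients. They would be larger if patients prone to relapse are also the ones lost. With unequal loss the direction is not fixed, so dropout patterns could drive the result. Because this affects the primary claim and can be changed before analysis, it should be corrected.

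**What to change.** State that last observation carried forward is not used for the primary endpoint. Estimate the 24-month failure or relapse risk in each arm by Kaplan-Meier with censoring at the last culture, or by multiple imputation using baseline and on-treatment data. Take the risk difference with its two-sided 90% confidence interval in both PP and mITT, and say how patients with incomplete follow-up are handled in each. The cultures scheduled every three months after treatment supply the data.

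Both estimates assume that loss is unrelated to outcome given the data used. Add a prespecified tipping-point analysis that worsens missing outcomes in the 4.5-month arms only. Counting all missing as unfavorable may be reported beside it, with the warning that it is not conservative here (Step 5).

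The cost is revised wording, a little programming and a slightly wider interval. No new data are needed.

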### Outcome measures

The primary efficacy outcome measures include the percentage of participants with treatment failure or relapse by 24 months after the end of treatment, percentage of participants with treatment failure at either 4.5 months or 6 months after randomization. The secondary efficacy and safety outcomes include the time to sputum (both smear and culture) conversion within intensive phase of 2 months and the percentage of participants with sputum conversion (both smear and culture) at the completion of treatment, the number of adverse reactions occurring on treatment and during the follow-up period, adherence to treatment and radiological manifestation transition. Of note, treatment failure was defined as sputum smear positive at the end of treatment and relapse after completion of treatment is defined as at least one positive culture in the scheduled follow-up visits in two years. Participants with negative cultures at the end of follow-up are considered to have had a favorable outcome. For all treatment failures and relapses, one culture of a sputum sample obtained before treatment and one culture of a sputum sample obtained after treatment failure or relapse are planned to store at −80 °C and the samples will be sent to national clinical TB reference lab in Beijing Chest Hospital for further research. The detailed observation schedule is present in Table 3.

**Table 3 Tab3:** Assessment schedule – for all patients recruited

Observation/Investigation		Screening	Treatment Phase (weeks)									Follow-up (Post-treatment phase, months)							
Study visits		0	2	4	6	8	12	16	19	22	26	3	6	9	12	15	18	21	24
Time window (days)			±3	±3	±3	±3	±7	±7	±7	±7	±7	±14	±14	±14	±14	±14	±14	±14	±14
Demographics		X																	
Written or witnessed informed consent		X																	
Patients eligible criteria judgement		X																	
Medical history and clinical assessment		X	X	X	X	X	X	X	X	X	X	X	X	X	X	X	X	X	X
Concomitant diseases and medication taken assessment		X	X	X	X	X	X	X	X	X	X	X	X	X	X	X	X	X	X
Randomized assignment		X																	
Efficacy evaluation																			
Bacteriological test	Sputum smear	X	X	X	X	X	X	X	X	X	X	X	X	X	X	X	X	X	X
	Sputum culture	X	X	X	X	X	X	X	X	X	X	X	X	X	X	X	X	X	X
X-ray		X				X			X		X		X		X		X		X
Safety evaluation																			
Complete blood count		X		X		X	X	X	X	X	X								
Urinalysis		X		X		X	X	X	X	X	X								
Hepatic and renal functions		X		X		X	X	X	X	X	X								
Electrocardiograph (ECG)		X		X		X	X	X	X	X	X								
Body weight		X	X	X	X	X	X	X	X	X	X	X	X	X	X	X	X	X	X
Adverse effect record			X	X	X	X	X	X	X	X	X	X	X	X	X	X	X	X	X
Others																			
Drug distribution log		X	X	X	X	X	X	X	X	X									
Drug retrieve log			X	X	X	X	X	X	X	X	X								

X indicates assessments required at particular visits

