### Clinical site monitoring and quality assurance

Family Health International 360 China office (FHI360) is responsible for monitoring data quality in accordance with trial Standard Operating Procedures (SOPs). Based on the monitoring plan, field visit and audit will be performed at different stages. All participant records, CRFs, and other source documents for the patients recruited in this study will be made available for review by the monitors. The investigator and staff are responsible for being present and available for consultation during scheduled site audit visits. A site field visit feedback will be sent to each study site made by authorized individuals. Investigators of each local site will be convened monthly via web-based remote conference system to share with the progress of study and discuss with the problems met during the trial searching for trouble shooting answers. Quality assurance (QA) procedures are carried out according to Quality Management documents. A review of these documents is undertaken by Quality Management Advisory Group (QMAG) of CTCTC. QMAG has the power to stop ongoing practices of any site which violates study protocol significantly and makes decision of its restarting or closing with respect to specific circumstance. Quality control (QC) procedures are performed at each study site by designated staff to guarantee all the practices comply with trial SOPs. Microbiology examinations are also under proper QC guideline developed by CTCTC. Moreover, Good Clinical Practice (GCP) training and appropriate Good Laboratory Practice (GLP) training will be provided for all staff involved in the trial; this will be a component of capacity strengthening of the trial.

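### Two adjacent outcome sentences conflict on an isolated positive follow-up culture, and the relapse sentence lets unconfirmed positives accumulate over eight tests

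*Protocol article*

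**What the plan says.** Everything below is in the protocol article. Under Outcome measures, a primary outcome is the "percentage of participants with treatment failure or relapse by 24 months after the end of treatment". The relapse part is then fixed: "relapse after completion of treatment is defined as at least one positive culture in the scheduled follow-up visits in two years". Table 3 marks a sputum culture at months 3, 6, 9, 12, 15, 18, 21 and 24 after treatment, so each patient has eight chances to meet that definition.

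The next sentence reads: "Participants with negative cultures at the end of follow-up are considered to have had a favorable outcome".

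One isolate from before treatment and one from after the event are to be stored for every failure and relapse, and "the samples will be sent to national clinical TB reference lab in Beijing Chest Hospital for further research". The article gives these paired isolates no role in classifying the outcome.

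On laboratory practice, the section on clinical site monitoring and quality assurance says only that "Microbiology examinations are also under proper QC guideline developed by CTCTC".

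For the design, the Sample size assumption section states that "the standard 6-month regimen has a 95% or higher sputum culture conversion rate", against 92.5% for a 4.5-month regimen, and that "a margin of noninferiority of 5% was used".

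**The concern.** Take a patient who is positive once, say at month 9, and negative at every later visit including month 24. The relapse sentence makes this patient an event. The next sentence makes the same patient a success. These are exactly the patients in whom a laboratory false positive or a transient positive is most likely, and their primary outcome is undetermined.

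If the relapse sentence is applied as written, one positive in eight is enough and no confirmation is asked for. False positives unrelated to treatment then add events to every arm. This has two consequences for a noninferiority comparison on the absolute difference. The variance grows, so power falls. The true difference is also diluted, because a patient who truly relapses cannot be counted twice, so a regimen at the margin looks slightly better than it is.

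**Working it through.** **Inputs from the article.** Unfavorable rates of 5% (control) and 7.5% (experimental) are the complements of the 95% and 92.5% in Sample size assumption. Those are stated as culture conversion rates; I take them as the planning basis for the primary outcome. The margin is 5 points, one-sided alpha 0.05, planned power 0.80, with 1,300 per arm, 20% lost or not assessable, and 5.5% primary resistance. Statistical analysis specifies a Wald interval. Table 3 gives eight follow-up cultures.

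**Assumed, not in the article.** A false-positive rate f per culture, equal across arms and independent across visits; I show 0.1%, 0.5% and 1%.

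**The plan's own figure.** n = (1.645 + 0.842)² × (0.95×0.05 + 0.925×0.075) / 0.025² gives 1,157 evaluable per arm. Dividing by 0.8 gives 1,447, and dividing also by 0.945 gives 1,531, so the stated 1,300 is not reproduced. That is a separate matter. Here I start from the 1,300: 1,300 × 0.8 = 1,040 assessable, or 1,300 × 0.8 × 0.945 = 982 with the resistance allowance.

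**Formulas.**
- False relapse over eight cultures: F = 1 − (1 − f)^8.
- Observed rate = p + (1 − p)F.
- Observed difference = true difference × (1 − F).
- Chance of declaring noninferiority = Φ[(0.05 − observed difference)/SE − 1.645], with SE = √[(p_c(1−p_c) + p_e(1−p_e))/n] at the observed rates.

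**No false positives, n = 1,040.** SE = 0.0106; Φ(0.025/0.0106 − 1.645) = 76%.

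**Reading A: the relapse sentence governs. Worked case f = 1%, n = 1,040.**
- F = 1 − 0.99^8 = 0.0773.
- Control: 0.05 + 0.95 × 0.0773 = 12.3%. Experimental: 0.075 + 0.925 × 0.0773 = 14.6%.
- The 2.5-point difference is observed as 2.31 points; SE = 0.0150; power = 56%.
- At a true 5-point excess (10% against 5%): 0.10 + 0.90 × 0.0773 = 17.0% against 12.3%, observed as 4.61 points; SE = 0.0155; chance of declaring noninferiority = 8.1%.

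| f (assumed) | F | Control rate | True 5 points seen as | Power, n = 1,040 | Type I error, n = 1,040 | Power, n = 982 |
|---|---|---|---|---|---|---|
| 0 | 0 | 5.0% | 5.00 | 76% | 5.0% | 74% |
| 0.1% | 0.8% | 5.8% | 4.96 | 73% | 5.4% | 71% |
| 0.5% | 3.9% | 8.7% | 4.80 | 63% | 6.7% | 61% |
| 1% | 7.7% | 12.3% | 4.61 | 56% | 8.1% | 54% |

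**Reading B: the favorable-outcome sentence governs.** Mainly a false positive at the last visit then counts, so F is about f. At f = 1%, n = 1,040:
- Control: 0.05 + 0.95 × 0.01 = 5.95%.
- A true 5-point excess is seen as 5 × 0.99 = 4.95 points.
- Power is 72% and type I error 5.4%.

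This keeps the true rates at 5% and 7.5%. It ignores a further cost of that reading: a genuine relapse that is negative again by month 24 would be counted as favorable.

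**With two positives required.** F2 = 1 − (1 − f)^8 − 8f(1 − f)^7. At f = 1%, F2 = 0.27%, the control rate is 0.05 + 0.95 × 0.0027 = 5.3%, and power with 982 per arm is 72.9% against 74.1% with no false positives. Demanding no intervening negative makes F2 smaller still. This assumes that no true relapse is missed and leaves out positives sent to adjudication.

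**The case against.** **The rate is assumed.** The article gives no false-positive rate. At 1%, false relapses (7.7%) would exceed the whole planned control event rate (5%), so that row is an illustration and not an estimate. At 0.1% the harm is modest. This stands: the direction follows from equal rates across arms, the size does not.

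**A reader might infer that the plan settles every single positive as relapse**, and so take 56% power and 8.1% type I error as its properties. The documents do not support that, because the next sentence says otherwise for the patients concerned. Under that sentence the effect is small.

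**A reader might also infer that cultures are read in about 35 laboratories, or without species identification.** Neither is established. Study design and oversight counts participating institutions, not culture laboratories. Species identification is laboratory detail that an article may leave to the full protocol, and a quality-control guideline is mentioned.

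**Bias towards noninferiority is the lesser effect.** At 1% the planned 2.5 points become 2.3. The larger effect is lost power, which works against declaring noninferiority. Success is also required in both the per-protocol and modified intention-to-treat analyses, so a single-test type I error is an upper bound for the joint rule. This stands.

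**An any-positive rule is objective and sensitive**, which matters in an open-label trial where up to 20% may be lost or not assessable and a confirming culture may never arrive. This is fair and shapes the fix, but it does not remove the conflict.

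**The full protocol may hold a confirmation rule.** It would then contradict a threshold that the article states outright, so this is more than condensed detail.

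**Conclusion.** The point holds in two parts. First, and independent of any assumption, an isolated positive followed by negatives through month 24 is both a relapse and a favorable outcome, and nothing in the article says which prevails.

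Second, if the relapse sentence governs, requiring only one unconfirmed positive among eight costs power and mildly inflates type I error. Over assumed rates of 0.1% to 1% per culture with 1,040 per arm, the power loss is about 3 to 20 percentage points and single-test type I error is 5.4% to 8.1%. If the other sentence governs, the loss at 1% is about 4 points of power, with type I error at 5.4%. These sizes rest on the assumed rate, equality across arms and independence across visits.

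The change is worth making before outcomes are classified. The article does not show that the trial is materially biased towards noninferiority.

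**What to change.** Replace the two sentences with one outcome-classification rule:

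- **Relapse:** two positive *M. tuberculosis* cultures from separate specimens after the end of treatment, without an intervening negative. The next scheduled culture can serve as confirmation.
- **Isolated positive followed by negative cultures:** not relapse.
- **Isolated positive that cannot be confirmed** (last available visit, loss to follow-up, or retreatment started): adjudication blind to arm, using the paired isolates already planned for the reference laboratory. Retreatment should not by itself define the event, because in an open-label trial that decision is made knowing the arm.
- **Sensitivity analysis:** the any-single-positive rule, reported alongside.

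This concerns outcome classification only, not patient management. It needs a change of endpoint wording and no extra visits. The costs are classification up to three months later, a few true transient relapses possibly missed, and some added work for the blinded adjudication.
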